### Data collection

Study data are managed with a password-protected electronic case report (CleanWEB™ operated by Telemedicine Technologies S.A.S., Boulogne-Billancourt, France).

#### Baseline data

The following baseline data are collected after the patient’s inclusion: sex, age, height, weight, BMI, American Society of Anesthesiologists (ASA) score, Euroscore II, smoking status, alcohol status, history of COPD or asthma with chronic inhalation therapy, lower respiratory tract infection in the past 3 months, abnormal preoperative chest x-ray, nutritional depletion (10% weight loss in the past 6 months), cardiovascular status (diabetes mellitus, arterial hypertension, preoperative atrial fibrillation, left ventricular ejection fraction, echocardiographic right ventricular distention defined by a right ventricle/left ventricle ratio > 1, history of stroke) and preoperative creatininemia > 200 μmol/L.

#### Intraoperative variables

During the surgery, the anesthesiologist in charge collects the following variables: type of surgery (coronary artery bypass graft, valve surgery, aortic surgery, mixed or complex surgery), need for mammary artery harvesting (unilateral or bilateral), CPB duration, aortic cross clamp duration, cardioplegia volume, intraoperative fluid volume including CPB priming (crystalloid and colloid), use of blood transfusions, need for intraoperative vasopressor (other than phenylephrine or ephedrine), need for inotropes during CPB weaning, effective tidal volume (milliliters and milliliters per kilogram of ideal body weight), intraoperative lowest, highest and main PEEP (main PEEP is defined as the PEEP used most of the time during surgery, as indicated on the ventilator monitor), complete realization of each recruitment maneuver, effective ventilation during CPB, need for protocol deviation (surgical or hemodynamic), need for rescue therapy for desaturation and calculated dynamic and static respiratory compliance at the end of surgery.

#### Postoperative variables

Respiratory assessment is carried out at least 2 h after extubation if the respiratory rate is > 10 cycles per minute. Then, patients are visited, twice a day, every postoperative day until postoperative day 7 in order to assess the presence of PPCs or secondary endpoints. Need for supplemental oxygen is assessed at every visit by measuring SpO2 and/or PaO2 after 10 min breathing room air. During the ICU stay, a daily chest x-ray is prescribed. In the surgical ward, a chest x-ray is prescribed at the discretion of the physician in charge. In the case of new or continued invasive mechanical ventilation, blood gas analysis is prescribed every 8 h in order to assess the PaO2/FiO2 ratio. In extubated patients, an arterial blood gas analysis is prescribed once a day during the ICU stay, and in the case of desaturation in the surgical ward. Echocardiography can be implemented at the discretion of the physician in charge of patient care, to diagnose cardiogenic pulmonary edema (Fig. 2).

### Sample size and power

The sample size was determined to obtain 80% power to detect a 10-point difference between the two groups in the occurrence of PPCs at day 7 (25% in the control strategy group vs 15% in the experimental strategy group). This difference is based on previous reports [1, 3, 10] and has been considered to be clinically significant. With the threshold for statistical significance set at a *P* value of 0.05, these calculations showed that 494 patients are needed (247 per group, Fig. 1). As patients will be allocated in the operating room after confirmation of the indication for surgery and followed during the 7 postoperative days in the ICU and surgical ward, a very low dropout rate is expected.

### Statistical analysis

The data will be analyzed using SPSS version 17.0 software. Patients who have at least one of the following conditions will be not included in the final analysis: patients inappropriately included despite providing consent, and patients who remove their consent. The primary analysis will be carried out according to the intention-to-treat principle. The full analysis population (including all subjects who will be randomized and will be at least evaluated at baseline) will be used in the primary analysis. No interim analysis is planned. A flow chart will be provided. The normality of the parameters will be estimated using frequency histograms and the Shapiro test. The baseline and intraoperative parameters will be described per group (“control” and “experimental”) in accordance with the Consolidated Standards of Reporting Trials (CONSORT) guidelines [40]. The proportion of PPCs at 7 postoperative days will be calculated and compared between the two groups (control and experimental) using the chi-square test or Fisher’s exact test for categorical variables (primary analysis). Multivariate analysis (secondary analysis) using logistic regression models will be performed to determine variables potentially linked to the occurrence of PPCs. Variables relevant to the models will be selected based on their clinical significance and/or a threshold *P* value ≤0.1 in the univariate analysis. The final models will estimate the odds ratios and 95% confidence intervals. The proportions of each secondary endpoint (each postoperative pulmonary complication, non-pulmonary complication, use of new invasive and non-invasive ventilation, use of high-flow nasal oxygen therapy, adverse event) will be compared between the groups. Multiple comparison corrections will be performed for non-independent outcomes. ICU-free days will be compared between the two groups. A potential center effect will be assessed by mixed effects modeling using generalized linear mixed model (SAS software, 9.4 version, GLIMMIX procedure; center as a random effect); the result will be presented as the odd ratio and its 95% CI. All of the tests will be two-tailed with a 5% significance level.

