#### Randomization

Computer-generated randomized lists will be drawn up by an independent operator before the beginning of the study, using a permuted block design. The allocation sequence is stratified by center (1:1 allocation ratio) and sequentially numbered. The allocation is implemented automatically in the electronic case report form (CleanWEB™, Telemedicine Technologies S.A.S., Boulogne-Billancourt, France). The anesthesiologist in charge will assign a patient to the intervention when the patient is in the operating room with a confirmed indication for surgery.

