#### Follow up

During transport from the operating room to the ICU, ventilation is operated with a self-inflating balloon or transport ventilator. If the transport ventilator is used, respiratory parameters are set according to the allocated treatment arm. A fast-track extubation protocol, defined by extubations performed before the 6th postoperative hour, is followed in all centers. The postoperative care, including sedation drugs, analgesia, fluid management, respiratory physiotherapy and the duration of the stay in the ICU, is performed according to local protocols and at the discretion of the physician in charge. The postoperative use of curative non-invasive ventilation or nasal high-flow oxygen therapy is implemented according to local protocols in each recruiting center. “Prophylactic” use (before any type of respiratory failure) of these techniques is not permitted. New invasive mechanical ventilation will be indicated at the discretion of the ICU physician in charge. The minimal ICU length of stay is 24 h.

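### Allocation is stratified by center but the primary chi-square or Fisher test is not: a valid test, slightly conservative if centers differ (minor)

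*Protocol article*

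**What the plan says.** Under Randomization, lists are drawn "using a permuted block design", and "The allocation sequence is stratified by center (1:1 allocation ratio) and sequentially numbered".

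Under Statistical analysis, the comparison reads: "The proportion of PPCs at 7 postoperative days will be calculated and compared between the two groups (control and experimental) using the chi-square test". The alternative named is Fisher's exact test, and the sentence labels this comparison as the primary analysis. No center term is mentioned.

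Center enters later in the same section: "A potential center effect will be assessed by mixed effects modeling using generalized linear mixed model", with center as a random effect, and "the result will be presented as the odd ratio and its 95% CI". That model is not called primary. The multivariable logistic models are labelled secondary and serve another purpose: "Multivariate analysis (secondary analysis) using logistic regression models will be performed to determine variables potentially linked to the occurrence of PPCs".

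Sample size and power gives 494 patients (247 per group) for 25% versus 15%, 80% power and a significance threshold of 0.05. Statistical analysis makes all tests two-tailed.

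**The concern.** When arms are balanced within each center, differences between centers cancel out of the treatment contrast. A crude chi-square still counts them in its variance. The test then rejects less often than its nominal level when there is no effect, and it uses the data less efficiently than a test stratified by the factor used in the randomization.

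Differences between centers are plausible. Under Surgery, anesthetic drugs, bypass management, fluids and transfusion follow local practice. Under Follow up, so do sedation, analgesia, physiotherapy and length of ICU stay. Under Postoperative variables, chest x-rays on the surgical ward are at the physician's discretion, and several PPC components need an x-ray.

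What is at stake is some efficiency in the primary P value. Protection against a false positive is not affected.

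**Working it through.** **Inputs from the protocol article.** 25% versus 15%, two-sided 5% level, 80% power, 247 per group (Sample size and power; Statistical analysis); 1:1 allocation in permuted blocks within center (Randomization).

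**Assumptions.** 2, 3, 5 or 8 centers of equal size; center log-odds SD from 0 to 1.0; a common odds ratio; arms exactly balanced within center.

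**1. The plan's own figure.** The unpooled normal formula gives, per group,

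n = (1.960 + 0.842)² × (0.25×0.75 + 0.15×0.85) / 0.10² = 7.849 × 0.315 / 0.01 = 247.2.

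This matches 247 per group and 494 in total. The pooled formula gives 250 per group. Power of the crude test at 247 per group is 79.5%. The stated sample size and power reproduce.

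**2. Why the crude test is conservative.** Under no effect, with K equal centers at rates p_k averaging p, the true variance of the difference is (2/n) × [p(1−p) − Var(p_k)]. The crude test uses (2/n) × p(1−p). With r = 1 − Var(p_k)/[p(1−p)], the actual type I error is 2 × [1 − Φ(1.96/√r)].

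- Two centers, SD 0.5, rates about 16% and 34%: Var = 0.09² = 0.0081; r = 1 − 0.0081/0.1875 = 0.957; 1.96/√r = 2.004; type I error about 4.5%.
- Two centers, SD 1.0, rates about 9% and 41%: Var = 0.16² = 0.0256; r = 1 − 0.0256/0.1875 = 0.863; 1.96/√r = 2.109; type I error about 3.5%.

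**3. Simulation.** There were 40,000 runs per setting. The null was 25% in both arms and the alternative 25% versus 15% overall. The unstratified Pearson chi-square was compared with Cochran-Mantel-Haenszel (CMH) stratified by center. Ranges are over 2, 3, 5 and 8 centers.

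| Center SD (log-odds) | Control rates, 5 centers | Type I error, crude | Type I error, CMH | Power, crude | Power, CMH | Power given up (points) |
|---|---|---|---|---|---|---|
| 0 | 25% | 4.8–5.3% | 4.8–5.2% | 79.5–79.7% | 79.6–79.8% | 0–0.1 |
| 0.3 | 17–34% | 4.8–5.1% | 4.9–5.3% | 79.5–80.2% | 80.0–80.6% | 0.4–0.5 |
| 0.5 | 13–40% | 4.4–4.6% | 4.9–5.1% | 80.0–80.4% | 81.1–81.5% | 1.1 |
| 0.8 | 8–48% | 3.9–4.0% | 5.0–5.2% | 80.6–81.1% | 83.1–83.7% | 2.5–2.6 |
| 1.0 | 6–53% | 3.2–3.5% | 4.8–5.1% | 81.2–81.8% | 84.5–85.2% | 3.3–3.7 |

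The Monte Carlo standard error is √(0.05×0.95/40,000) ≈ 0.1 point for type I error and √(0.8×0.2/40,000) = 0.2 point for power. The two-center simulated values, 4.57% at SD 0.5 and 3.45% at SD 1.0, agree with the hand calculation.

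The crude test never falls below about 79.5% power. What is lost is the extra power that a stratified test would deliver from the same patients.

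**The case against.** The strongest reply is that nothing is broken. The crude test keeps its level at or below 5%. The sample size was calculated for an unstratified two-proportion comparison, so test and calculation agree, and the planned power is delivered. A center-adjusted model is already specified, down to procedure and random effect. All of this stands, and it keeps the point minor.

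The size of the gain also rests on assumptions. At SD 0.8 to 1.0, control rates across five centers would run from below 10% to about 50%, and nothing in the document supports a spread that wide. Surgeons work in high-volume university centers, and the ventilation, fast-track extubation, PPC definitions and twice-daily checks are common to all centers. The smaller losses in the table are therefore at least as plausible as the larger ones.

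Local practice on respiratory support ("The postoperative use of curative non-invasive ventilation or nasal high-flow oxygen therapy is implemented according to local protocols in each recruiting center") is weak evidence of center differences in the endpoint. The Discussion explains that the need for these techniques was kept out of the primary outcome for that reason.

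Three stronger readings are tempting, and the document does not support them:

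- That it is unclear whether the crude P value or the center-adjusted odds ratio carries the conclusion. Statistical analysis labels the chi-square or Fisher comparison as primary, which settles it.
- That adjustment for baseline covariates would add several points of power. That gain is unrelated to center, and its size would depend on an assumed prognostic strength that the document does not give.
- That the absence of a risk difference with its interval is an error. A condensed article may leave the effect measure to an analysis plan that is not shown.

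What the reply does not remove is the mismatch: the article names the randomization stratum and names a primary test that ignores it.

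**Conclusion.** The point holds, and its severity is minor. The primary test does not reflect the center-stratified allocation. If PPC rates differ between centers, it is valid but slightly conservative. For 2 to 8 equal centers and a log-odds SD of 0 to 1.0, its type I error averages about 5.0% falling to 3.3%, and it forgoes about 0 to 3.5 power points. At SD 0.5 the loss is about 1 point, and without center differences it is nil. The number of centers and their spread are assumptions, because the text at hand gives neither.

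A reader might infer that the trial is underpowered, that 494 is wrong or that the primary P value is unsafe. None of these follows: 494 reproduces, crude-test power stays at about 80% throughout, and any error in level is in the cautious direction.

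**What to change.** Name the Cochran-Mantel-Haenszel test stratified by center as the primary analysis, reported with the Mantel-Haenszel risk difference and its 95% CI. This also puts the estimate on the scale used for planning. The center-adjusted mixed model already planned could be made primary instead. CMH is simpler and does not need a center variance estimated from what may be few centers. Keep the unstratified chi-square as a supportive analysis.

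The cost is a change of wording in the protocol or analysis plan and a few lines of code. Center is already recorded as the randomization stratum, so no new data are needed and the sample size stays at 494. The article describes the trial as still recruiting with no interim analysis planned, so the change can be documented before any comparison by arm.

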### Regulatory issues

An ethics committee approved this study (Comité de Protection de Personnes Sud Mediterranee I) on 29 February 2016 (ID RCB 2016-A00352–49). The study was registered on ClinicalTrials.gov on 15 August 2016 (NCT02866578). All eligible patients will be included in the study after obtaining signed, informed consent. At any time and for any reason, the patient can withdraw his consent. Investigators are able to terminate the study prematurely in a patient’s best interest. Should the study be discontinued, the reason will be documented on the electronic case report form. Patient data are collected anonymously on the electronic platform, as an identification number designates them. All severe adverse events are documented in the electronic case report form and declared to the Comité de Pharmacovigilance Assistance Publique des Hôpitaux de Marseille. Patient data and safety are monitored by a monitoring referent ([name]) and a monitoring committee ([name], [name], [name]). [name] will conduct monitoring visits independently. Full access to the final data set will be reserved for the main investigator (DL) and the statistician (KB) under the control of the monitoring committee.

## Discussion

Despite recent technological progress, cardiac surgery with CPB remains responsible for a high rate of respiratory morbidity [1]. This specificity results from a “two-hit” lung injury [10]. A specific pulmonary inflammation and ischemia-reperfusion injury is associated with the usual adverse effects of general anesthesia and invasive mechanical ventilation [5]. Protecting the lung during general anesthesia with specific ventilator settings has already been described. For example, the use of low tidal volumes (6–8 mL/kg of ideal body weight) has been well-validated in different types of surgery [23]. However, the use of low tidal volumes may be responsible for the development of atelectasis, particularly in the dependent region of the lung [16]. The open-lung ventilatory approach is based on systematic alveolar recruitment in order to prevent atelectrauma and increase pulmonary compliance. In parallel, the use of high levels of PEEP is necessary for maintaining this benefit [24]. Continuing to ventilate the lung during CPB, despite the absence of perfusion, can reasonably be integrated into the open-lung approach in order to prevent the formation of atelectasis during this surgical step [14]. In abdominal surgery, the benefit of the open-lung approach, in terms of PPC prevention, has not yet been proved [28, 29]. Moreover, the use of high levels of PEEP and/or lung ventilation during CPB may interact with the surgical technique, adding complexity to the surgical procedure and reducing surgical comfort. The fact that low PEEP ventilation and ventilation cessation during CPB make the surgical procedure easier has been claimed by a vast majority of cardiac surgeons. This observation may explain current practices in mechanical ventilation in cardiac surgery operating rooms [31]. Finally, the hemodynamic impact of open-lung ventilation could be more challenging for cardiac anesthesiologists. Because of its pathophysiological specificities, cardiac surgery involves a high incidence of PPCs and might particularly benefit from the open-lung approach [25, 26, 32]. However, because of a real surgical concern, the use of the open-lung approach in these patients needs to be supported by the highest level of clinical evidence that will guide the anesthesiologists and cardiac surgeons in managing ventilator settings before, during and after the CPB. The PROVECS trial is the first multicenter, randomized, controlled trial to evaluate the effect of a perioperative and multimodal ventilatory strategy depending on the open-lung approach in cardiac surgery with CPB. For feasibility concerns, specific surgical protocol deviations have been designed. The objective is thus to compare an experimental, surgeon-controlled, open-lung strategy with a conventional, low PEEP and “surgeon-friendly” approach as the control strategy.

In the experimental arm, we have chosen a multimodal approach, from intubation to extubation, in order to maximize the potential benefit effect of alveolar recruitment. Indeed, the risk of atelectasis persists during the entire mechanical ventilation period. The pressure level for recruitment maneuvers is relatively low (30 cmH2O) for hemodynamic reasons. However, by timing two recruitment maneuvers under CPB, we ensure good hemodynamic tolerance of these maneuvers. Moreover, this level of pressure prevents unintended lung harm with regard to the risk of higher transpulmonary pressures when the thorax and/or pleura are opened. The PEEP levels in each group have been empirically defined. We did not choose an individualized PEEP titration protocol because of the absence of a validated reference titration protocol and because of the high risk of hemodynamic intolerance and barotrauma [27]. In the open-lung group, the basal PEEP level of 8 cmH2O is moderate in comparison with previous studies in non-cardiac surgery [28, 29]. This will reduce the risk of lung overdistension and higher driving pressures [41]. Nonetheless, this starting level of PEEP is high enough to both prevent atelectrauma and be significantly different from the control group’s level (2cmH2O) considering the probable surgical protocol deviation. On the other hand, in the control group, the conventional ventilatory protocol corresponds in many ways to recent reports of current practices in mechanical ventilation in cardiac surgery [31] and makes possible optimal surgical comfort. During CPB, the use of ultraprotective ventilation with very low tidal volumes has been selected because of the theoretical advantages of this approach shown in previous studies of postoperative shunt fraction and inflammatory response [32]. Setting FiO2 at 40% during CPB has been planned in order to prevent absorption atelectasis secondary to lung denitrogenation while maintaining lung oxygenation by direct diffusion of alveolar oxygen [36].

The experimental arm design includes standardized protocol deviations on surgical demand. This is a crucial point. The strict application of the open-lung strategy in cardiac surgery is unrealistic and could lead to surgical complications for participating subjects. The objective of this trial is to evaluate the impact of maximizing alveolar recruitment in an intention-to-treat way. Full collaboration is therefore necessary between the anesthesiologist and the surgeon in order to adapt ventilator settings and ensure acceptable surgical comfort. The effective intraoperative settings will be registered and analyzed, and the results will be interpreted to determine the effective differences between the two groups. In this regard, we think that a per protocol analysis is not necessary because of its clinical irrelevance. The study population corresponds to daily elective surgical cases. We exclude emergent or redux surgery, and patients with severe preoperative cardiac disease because of the high risk of confounding factors in PPC assessment. The risk of hemodynamic intolerance and the complexity of the surgical procedures in these cases may lead to major protocol deviation, thus diminishing the relevance of the trial.

We opted for a binary collapsed composite of single PPCs that have a real clinical meaning in daily practice. With a consensual and unambiguous definition of PPCs, we facilitate the assessment of the primary outcome, prevent the risk of wrong diagnoses and allow for comparisons with previous or ongoing studies [20, 28, 29, 37]. For example, the “respiratory failure” outcome, based on hypoxemia evaluated with SpO2 tolerance to room air ventilation, has previously been described in different trials interested in PPCs. This is a very pragmatic definition, clinically relevant for physicians caring for patients undergoing cardiac surgery. As the relevance of the primary endpoint depends on its definition, we insist on external validity and the objective way of diagnosing each PPC used in the composite endpoint of this trial. We have chosen to exclude pneumothorax and to evaluate it as an adverse event because high PEEP may increase the incidence of pneumothorax (barotrauma or surgical trauma). Cardiogenic pulmonary edema is considered to be an extrapulmonary complication because it may bias the primary outcome regarding the potential high incidence of this event in patients with chronic heart diseases. We insist on strict confirmation of cardiogenic edema with high left atrial pressure estimated with echocardiography or a pulmonary artery catheter. Nonetheless, pneumothorax and cardiogenic pulmonary edema might lead to the primary outcome discovering whether or not they lead to hypoxemia. The need for non-invasive ventilation or high-flow nasal oxygen therapy has not been included in the primary outcome because of the absence of defined indications in the standard procedures of the trial. Curative non-invasive ventilation or high-flow nasal oxygen therapy are used depending on local protocols or the physician’s discretion. Therefore, it will be recorded as a secondary outcome. By not allowing prophylactic use (in the absence of hypoxemia) of these techniques, we avoid a potential interaction with the primary outcome. Finally, we will evaluate postoperative extra-pulmonary complications because PPCs may be related to other organ failures, such as sepsis, postoperative atrial fibrillation or acute kidney injury. Evaluating different surgical complications (such as acute postoperative bleeding with a need for re-intervention, pericardial tamponade, wound infection, or the need for high doses of inotropes) will give a safety point of view on the surgical impact of the open-lung approach.

In conclusion, the PROVECS multicenter, randomized, controlled trial aims to evaluate the impact of an open-lung multimodal and perioperative ventilatory approach on the incidence of PPCs after on-pump cardiac surgery. The strategy evaluated is optimized with regards to patient safety and surgical comfort in order to be clinically relevant. The pragmatic design of this trial will ensure that the results have a strong impact on the clinical practice of cardiac anesthesiologists and cardiac surgeons.

